**Results:**

Study recruitment began in August 2021 and, with several disruptions owing to COVID-19, is expected to be completed by December 2023.

**Conclusions:**

This study will provide a better understanding of the factors associated with dyspnea and the feasibility and effectiveness of IMT combined with standard-of-care rehabilitation. IMT may be a novel therapeutic strategy for improving respiratory muscle function and patient-reported outcomes in individuals with hEDS or G-HSD.

**Trial Registration:**

ClinicalTrials.gov NCT04972565; https://clinicaltrials.gov/ct2/show/NCT04972565

**International Registered Report Identifier (IRRID):**

DERR1-10.2196/44832

## Introduction

### Background

Ehlers-Danlos Syndrome (EDS) is a group of hereditary connective tissue disorders characterized by multisystem manifestations involving musculoskeletal and nonmusculoskeletal domains [1]. Currently, the International Classification of EDS and related disorders includes 14 subtypes based on a set of clinical criteria, with the most common subtype being hypermobile EDS (hEDS), which comprises 80% to 90% of EDS cases [1-3]. Patients who present with symptomatic generalized joint hypermobility and chronic pain but do not meet the International 2017 classification criteria are classified as having generalized hypermobility spectrum disorder (G-HSD) [3]. The clinical manifestations of the disease vary according to the EDS subtype, and our understanding of this disorder has evolved to recognize multisystem manifestations beyond the musculoskeletal system, including gastrointestinal, neurological, cardiovascular, and respiratory involvement [1]. These manifestations arise from abnormal collagen or proteins that bind collagen that affect the connective tissue throughout the body [1]. Given the multisystem nature of hEDS and G-HSD, several symptoms such as pain and fatigue may contribute to reduced health-related quality of life (HRQL), physical deconditioning, anxiety, and depression [4-8].

### Respiratory Manifestations in EDS and G-HSD

Our research group and others have recently highlighted that respiratory manifestations are common in hEDS and G-HSD and include, but are not limited to, dyspnea, cough, asthma, and respiratory muscle weakness [2,9]. The collagen abnormalities lead to impairments throughout the respiratory system, which may contribute to the respiratory abnormalities observed in this population [2,10]. In individuals with hEDS, the prevalence of dyspnea is estimated to be approximately 50% [11]. Dyspnea has been described in a few studies on individuals with G-HSD, but its prevalence and determinants have not been well characterized [12]. A study reported that up to 26% of the patients with G-HSD presented with cardiorespiratory manifestations such as dyspnea, palpitations, and chest pain, which were commonly attributed to autonomic dysfunction [13].

Respiratory symptoms in EDS and G-HSD have also been associated with worse outcomes such as lower physical activity levels and function. Individuals with EDS or G-HSD experienced increased dyspnea while walking on a flat level compared with healthy controls [12]. Furthermore, a study investigating physical activity levels between patients with hEDS or G-HSD with autonomic dysfunction and those without autonomic dysfunction observed that autonomic dysfunction was associated with exercise intolerance, which is often attributed to increased symptoms of dyspnea and chest pain [14]. Postural orthostatic tachycardia syndrome, a more severe form of autonomic dysfunction, has also been observed to be associated with dyspnea, chest pain, and impairments in HRQL [15,16]. Thus, respiratory manifestations in individuals with hEDS or G-HSD have important consequences on exercise tolerance, HRQL, and functional abilities.

### Contributors to Dyspnea in hEDS and G-HSD

Functional impairments in respiratory muscle weakness occur in >75% of individuals with hEDS and can result in dyspnea and a restrictive pattern of ventilation [11]. The diaphragm is the main respiratory muscle, and alterations in collagen can lead to impairments in the respiratory muscle structure and function [17]. Respiratory muscle weakness has also been associated with lower vital capacity, which may contribute to dyspnea [18,19]. Thus, strengthening the respiratory muscles through modalities such as inspiratory muscle training (IMT) may improve dyspnea and pulmonary function [20].

Some individuals with hEDS or G-HSD have been observed to have chest wall deformities and increased rates of asthmatic symptoms, which can contribute to dyspnea and peripheral airway abnormalities [12,21,22]. There is also an increased tendency for dynamic airway collapse despite normal chest imaging, which highlights altered lung mechanics, including airway pressures and lung volumes [12]. Furthermore, deconditioning has been described as a contributor to low physical activity levels in the population with EDS or G-HSD as a consequence of increased joint laxity, pain, and peripheral muscle weakness [23]. Physical deconditioning may further exacerbate dyspnea and contribute to low exercise tolerance [23]. In conditions such as chronic obstructive pulmonary disease (COPD), cortical neural activity in the prefrontal cortex (PFC) has been shown to be associated with dyspnea and exercise intolerance and may be another contributor to dyspnea in hEDS or G-HSD [24,25]. Modalities such as functional near-infrared spectroscopy (fNIRS) have been used to assess PFC activity in individuals experiencing dyspnea during exercise testing [24]. Taken together, respiratory muscle weakness, peripheral airway changes, physical deconditioning, and autonomic dysfunction may contribute to the multifactorial nature of dyspnea in hEDS or G-HSD. These factors can be evaluated clinically and may help us understand the mechanisms that contribute to dyspnea and, importantly, tailor effective respiratory management strategies.

### IMT and Standard-of-Care Rehabilitation

IMT has been established as an effective intervention for improving respiratory muscle structure and function in populations with chronic lung diseases [26,27]. A study observed that among 104 individuals with hEDS, 80 (77%) individuals had respiratory muscle weakness [11]. After 6 weeks of IMT, respiratory muscle strength measured with sniff nasal inspiratory pressure improved by 20% (pre-IMT intervention: mean 41, SD 17 cm H_2_O vs post-IMT measurement: mean 49, SD 18 cm H_2_O; *P*<.001) in patients with hEDS. Furthermore, the 6-minute walk distance improved by 13% (pre-IMT measurement: mean 455, SD 107 m vs post-IMT measurement: mean 515, SD 127 m; *P*=.003) along with forced expiratory volume in 1 second by 10% (pre-IMT measurement: mean 94%, SD 14% vs post-IMT measurement: mean 103%, SD 11%; *P*=.01). Thus, IMT may be an effective intervention for improving respiratory muscle strength, lung function, and exercise capacity in patients with hEDS or G-HSD.

Physical rehabilitation involving whole-body exercises such as aerobic and strength training has been shown to improve dyspnea in healthy populations and populations with chronic lung diseases such as COPD and idiopathic pulmonary fibrosis [28-31]. In a meta-analysis of 14 randomized controlled trials (RCTs), resistance training and endurance training were associated with improved dyspnea tolerance during exercise training, along with resting dyspnea levels, in patients with COPD [30]. This is often attributed to improved physical fitness owing to exercise training, which increases the efficiency of the muscles and decreases the level of ventilatory demand [30]. Unlike other populations, research on the effects of exercise training on individuals with hEDS or G-HSD is in its early stages, with only 5 RCTs performed in this area to date [32]. Following rehabilitation, in patients with hEDS or G-HSD, improvements have been observed in exercise capacity, muscle strength, mood, HRQL, and performance of daily activities [32].

Although the IMT RCT highlighted the safety and feasibility of IMT in hEDS, the study did not evaluate the mechanisms of dyspnea or assess diaphragm structure and function [11]. Furthermore, physical activity and other concurrent training, which may provide synergistic beneficial effects on respiratory symptoms and exercise capacity, were not considered. Several studies on chronic lung disease have demonstrated that IMT in combination with whole-body exercises, such as aerobic exercise, offers synergistic benefits on respiratory muscle strength and endurance and exercise capacity in comparison with whole-body exercises alone [23,33,34]. IMT alone has been shown to be an effective intervention in populations with asthma, populations with COPD, and populations with interstitial lung disease for improving maximal inspiratory pressure (MIP), respiratory muscle endurance, and diaphragm function [26,27,35] and thus may be an effective strategy in the population with hEDS or G-HSD.

The efficacy of both IMT and standard-of-care rehabilitation in ameliorating dyspnea and improving aerobic capacity and respiratory muscle structure and function in the population with hEDS or G-HSD has not been investigated to date. It is also unclear whether IMT in combination with standard-of-care rehabilitation is a feasible intervention, specifically for the population with hEDS or G-HSD, given the increased comorbidities. Furthermore, the efficacy of IMT has only been evaluated in hEDS and yet to be studied in G-HSD. This study aims to address these gaps.

### Study Aims

The aims of this study are (1) to compare respiratory muscle strength and patient-reported outcome measures (PROMs) between individuals with hEDS or G-HSD and healthy, age- and sex-matched controls, as well as evaluate the main contributors to dyspnea in individuals with hEDS or G-HSD, and (2) to assess the feasibility of an RCT of IMT and standard-of-care rehabilitation (aerobic, resistance, neuromuscular stabilization, and balance and proprioception exercises) for improving respiratory muscle strength, exercise capacity, and PROMs compared with standard-of-care rehabilitation in hEDS or G-HSD.

### Hypotheses

We hypothesize that (1) individuals with hEDS or G-HSD will have lower respiratory muscle strength, higher peripheral airway resistance, lower HRQL, and higher anxiety and depression levels than age- and sex-matched healthy controls and that (2) the delivery of IMT and standard-of-care rehabilitation will be feasible and result in a significant improvement in respiratory muscle strength (MIP) over an 8-week period.

## Methods

### Study Design

Participants with hEDS or G-HSD will complete assessments at baseline (T_0_; Table 1) and will be randomized into the intervention arm (IMT and standard-of-care rehabilitation) or usual care group (standard-of-care rehabilitation). The standard-of-care rehabilitation at the GoodHope EDS Clinic at Toronto General Hospital comprises active exercise training involving aerobic, resistance, neuromuscular stabilization, and balance and proprioception exercises, and is a part of the GoodHope Exercise and Rehabilitation Program (GEAR) [36].

Age- and sex-matched healthy controls will undergo the same T_0_ assessments as those that the EDS and G-HSD intervention and usual care groups will undergo. The respiratory muscle structure and function, dyspnea, exercise capacity, and collected PROMs will be compared. Only the participants with hEDS or G-HSD (intervention and usual care groups) will repeat the T_0_ assessments after 8 weeks, as described in the subsequent section on assessments.

**Table 1 table1:** Summary of study measurements.

Measurement		Baseline assessments^a^	
		Intervention and usual care groups	Healthy control group
**Dyspnea**			
	Medical Research Council Dyspnea Scale	✓	✓
	18-Point Qualitative Dyspnea Scale	✓	✓
**Pulmonary function tests**			
	Oscillometry	✓	✓
	Spirometry and lung volumes	✓	✓
	Respiratory muscle endurance^b^	✓	✓
	Maximal respiratory pressures	✓	✓
	Diaphragmatic measures	✓	✓
**PROMs^c^**			
	Health-related quality of life: Short Form-36	✓	✓
	Mood: Depression, Anxiety, and Stress scale	✓	✓
	Physical activity volume: Godin Leisure-Time Exercise Questionnaire	✓	✓
	Demographic questionnaire	✓	✓

^a^All baseline measures will be repeated after 8 weeks for the participants with hypermobile Ehlers-Danlos Syndrome or generalized hypermobility spectrum disorder.

^b^Respiratory muscle endurance will be repeated at 4 weeks.

^c^PROM: patient-reported outcome measure.

### Ethics Approval

Ethics approval has been obtained from the research ethics board at the University Health Network (ID: 20-6346.0) and University of Toronto (ID: 42667). The study has been registered at ClinicalTrial.gov (NCT04972565).

Written informed consent will be obtained from all participants before the commencement of any research activities. The Standard Protocol Items: Recommendations for Interventional Trials, the CONSORT (Consolidated Standards of Reporting Trials) statement, and the Consensus on Exercise Reporting Template will be used [37-39]. Refer to Figure 1 for the CONSORT flow diagram.

**Figure 1 figure1:**
[figure not shown]
CONSORT (Consolidated Standards of Reporting Trials) flow diagram with healthy controls. GEAR: GoodHope Exercise and Rehabilitation Program; G-HSD: generalized hypermobility spectrum disorder; hEDS: hypermobile Ehlers-Danlos Syndrome; IMT: inspiratory muscle training.

### Recruitment and Screening

Participants with hEDS or G-HSD will be recruited from the GEAR program at Toronto General Hospital, which is a major teaching hospital in Toronto, Canada. The GEAR program evaluates approximately 12 new participants per month. Potential participants are screened for study eligibility by exercise professionals who are part of the GEAR program. The research team will confirm the eligibility criteria, discuss study participation, and obtain consent among interested participants. The study flow of participants is shown in Figure 1.

### Participants With hEDS or G-HSD

The sample will comprise adult individuals (aged ≥18 years) diagnosed with hEDS or G-HSD by the EDS medical team at Toronto General Hospital based on the 2017 diagnostic criteria [3]. Participants will be included if they have started their participation in the GEAR program within 4 weeks.

The following exclusion criteria will be applied:

Diagnosis of other subtypes of EDS (eg, classical and vascular)Have a cardiac pacemaker, defibrillator, neuromuscular disease, severe autonomic dysfunction, or other cardiovascular manifestations limiting exercise or other exercise contraindicationsRecent respiratory infection (<1 month) or known diagnosis of obstructive or restrictive parenchymal diseaseHistory of pneumothorax, acute otitis media (fluid behind the eardrum), or rupture of tympanic membranes, given the risk owing to IMTParticipation in formal exercise training or IMT program within the last 3 monthsInsufficient English fluency to provide informed consent or inability to follow study protocolsSelf-reported pregnancyNo internet access for IMT or web-based assessments

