### Healthy Controls

Healthy adults (aged ≥18 years) will be age- and sex-matched with the participants with EDS and G-HSD. Individuals will be excluded from the study if they meet the following criteria:

Diagnosis of a respiratory, cardiovascular, or musculoskeletal condition that may contribute to exercise limitationPresence of cardiac pacemaker or implantable defibrillatorInsufficient English fluency to provide informed consent or inability to follow study protocolsSelf-reported pregnancyActive smoker (cigarettes or marijuana)

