### Sociodemographic Parameters

We will abstract information on demographics such as age, ethnicity, sex, employment status, education level, and lifestyle factors (eg, smoking status) from the medical charts for the participants with hEDS or G-HSD. Demographic data will be collected from healthy controls via a demographic survey.

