### Statistical Analysis

#### Proposed Data Analyses

For objective 1, we aim to compare respiratory muscle structure and function and PROMs between patients with hEDS or G-HSD and healthy controls and to evaluate the main correlates with dyspnea in patients with hEDS or G-HSD. Descriptive statistics will be used for continuous variables (mean and SD or median and IQR), and frequencies will be used for categorical variables. We will use multivariable regression analysis to compare any differences between groups across respiratory parameters and PROMs, adjusted for EDS subtype (hEDS or G-HSD). We will explore the associations with peak Borg dyspnea scores during CPET using multivariable regression, with possible determinants being MIP, diaphragm thickening fraction, PFC activity, and PFT parameters.

For objective 2, we aim to assess the feasibility of IMT and standard-of-care rehabilitation for improving respiratory muscle strength, exercise capacity, and PROMs compared with standard-of-care rehabilitation alone in patients with hEDS or G-HSD. Descriptive statistics will be used to summarize program adherence, recruitment, participant satisfaction, attrition, and safety in the hEDS or G-HSD study groups. Estimates of within- and between-group differences at T_0_, 4 weeks, and 8 weeks will be reported using means and 95% CI. Paired *t* tests and *t* tests will be used to compare the changes in the primary pilot outcome (MIP) and secondary measures over the 8-week study period within and between the 2 randomized groups.

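### The patient and healthy-control groups are selected by different rules on smoking, recent training and recent infection, so part of the objective 1 difference can reflect selection rather than hEDS/G-HSD

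*Protocol article*

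**What the plan says.** The planned contrast is in the protocol article under Study Design: "The respiratory muscle structure and function, dyspnea, exercise capacity, and collected PROMs will be compared". The Hypotheses section predicts lower respiratory muscle strength, higher peripheral airway resistance, lower HRQL and more anxiety and depression in patients.

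The eligibility lists differ in three places:

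- **Smoking.** The Healthy Controls section excludes an active "smoker (cigarettes or marijuana"). The section on participants with hEDS or G-HSD has no smoking rule.
- **Training.** Patients are excluded for participation in "formal exercise training or IMT program within the last 3" months. Controls have no such rule.
- **Infection.** Patients are excluded for a recent "respiratory infection (<1 month) or known diagnosis" of parenchymal lung disease. The nearest control rule covers diagnosed conditions that may limit exercise and does not name recent infection.

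Controls "will be age- and sex-matched with the participants with EDS and G-HSD", and no other matching factor is named. Under Proposed Data Analyses, regression is to "compare any differences between groups across respiratory parameters and PROMs, adjusted for EDS subtype (hEDS or G-HSD"). Smoking is recorded, as "lifestyle factors (eg, smoking status) from the medical charts for the participants with hEDS or G-HSD", while controls complete a demographic survey. It is not named as a covariate in this comparison.

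**The concern.** A patient-control comparison isolates the diagnosis only if the groups are otherwise drawn by the same rules, or if the differences are handled in the analysis. Here neither is stated. Smoking is not part of hEDS or G-HSD, yet it is permitted in one group and barred from the other. It bears directly on airway resistance and lung function, and it pushes in the direction that the first hypothesis predicts. Recent formal training is barred in patients and permitted in controls, which can widen a difference in exercise capacity. Recent infection is barred only in patients, which tends to shrink the difference.

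At stake is the reading of one of the study's two aims. A modest difference in oscillometry, spirometry or peak aerobic capacity could be reported as a feature of the disease when part of it comes from who was allowed in.

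**Working it through.** **1. The plan's own figure.** The Sample Size section (objective 1) assumes that 75% of patients and 25% of controls report a Borg score of 4 or more, with 34 v 17 participants and α = .05, and states 90% power. The continuity-corrected two-proportion formula (two-sided, 2:1) requires 34 patients and 17 controls for 90% power, so the figure reproduces. The sample size is not in question.

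**2. Can the named adjustment help?** Patients are either hEDS or G-HSD; controls are neither. Subtype is therefore nested within patient status, and the model amounts to a three-group comparison: controls, hEDS, G-HSD. Smoking, training and infection history appear nowhere in it, so a patient-control imbalance in any of them passes straight into the group difference.

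**3. Size of a smoking bias, continuous outcome.** The documents give no smoking rate and no smoking effect. Both inputs are assumptions: a proportion *s* of patients smoke, and smokers score *d* SD worse. No control smokes.

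- Bias = *s* × *d*. Low end: 0.10 × 0.5 = 0.05 SD. High end: 0.25 × 0.8 = 0.20 SD.
- Standard error of a standardised difference = √(1/34 + 1/17) = 0.297.
- Noncentrality = bias / 0.297, which is 0.17 at the low end and 0.67 at the high end.
- Rejection by a two-sided 5% t test with 34 + 17 − 2 = 49 df and no true disease effect: 5.3% at 0.05 SD and 10.1% at 0.20 SD.

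**4. The same question for the powered dyspnea contrast.** Assume a 25% base rate of Borg ≥4 in both groups, 10% to 30% smokers among patients, and a rate of 35% to 60% in smokers.

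- Lowest spurious difference: 0.10 × (0.35 − 0.25) = 1 percentage point.
- Highest: 0.30 × (0.60 − 0.25) = 10.5 points.
- Chi-square rejection runs from 4.6% to 10.3%, against 4.7% with no bias.

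The study is powered for 75 − 25 = 50 points, so this contrast is little exposed. Smaller differences are the ones at risk.

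**5. Training.** The patient list also states: "Participants will be included if they have started their participation in the GEAR program within 4 weeks". Study Design describes GEAR as active exercise training. Patients may therefore already be up to 4 weeks into a programme at baseline, and the article does not say how that fits with the 3-month training exclusion; the two rules must be reconciled. The net training contrast with controls cannot be sized from the documents.

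**6. Infection.** No rates are given. The direction is opposite to smoking, and nothing shows that the two cancel.

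**7. Cost of restricting to non-smoking patients.** 10% of 34 is 3.4 and 25% is 8.5, so about 3 to 9 patients would be dropped.

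| Patients v controls | SE | Ratio to 34 v 17 |
|---|---|---|
| 34 v 17 | 0.2970 | 1 |
| 31 v 17 | 0.3018 | 1.016 |
| 25 v 17 | 0.3144 | 1.058 |

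**The case against.** Several points on the other side have force.

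- **Some of the asymmetry has a purpose.** Barring prior training or IMT in patients suits the randomized comparison, and the abstract says that controls supply normative values, for which a non-smoking group is a recognisable choice. This stands as an explanation. It does not make the two groups comparable for objective 1.
- **Deconditioning may be part of the disease.** The introduction describes it as a consequence of joint laxity, pain and weakness. Selecting or adjusting on activity therefore changes the question. This stands, and is why training belongs in a sensitivity analysis only. It does not apply to smoking.
- **Known parenchymal lung disease is excluded in patients.** That removes patients whose smoking has already led to such a diagnosis, but not smokers without one.
- **Activity is visible.** Godin scores are taken in both groups, so an imbalance could be seen. They are not named in the comparison.

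A reader might infer more than the text supports. One inference is that selection differences will be mistaken for disease effects; without rates, only that they can be. Another is that patients are untrained and controls trained; the GEAR entry window makes that uncertain. A third is to add a training bias to the smoking bias. Totals of 0.3 and 0.4 SD would give rejection of 17% and 26%, but they need an assumed training effect on exercise capacity, which the first hypothesis does not list, and they ignore the opposing infection rule. Finally, nothing shows that charts miss marijuana use. Table 1 also ticks a demographic questionnaire for patients, and an article need not print its items.

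**Conclusion.** The point holds for objective 1. The three asymmetries and the single, ineffective adjustment are explicit in the text, so they are not details left to an unseen analysis plan. Smoking is the clearest problem: it is barred in one group only, is not part of the disease, and favours the hypothesis.

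Under the assumptions shown, smoking adds 0.05 to 0.20 SD and raises a nominal 5% error rate to between about 5% and 10%. That is negligible at the low end and a doubling at the high end. The training contribution is uncertain in size, and infection works the other way. The 50-point dyspnea contrast is unlikely to be overturned; modest differences in airway resistance, lung function and exercise capacity are exposed. The randomized comparison and the feasibility outcomes are not affected. This is a cheap improvement worth making, not a flaw that invalidates the study.

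**What to change.** 1. Prespecify the objective 1 patient-control comparisons in patients who are not active smokers of cigarettes or marijuana, mirroring the control rule, and report the result for all patients alongside.
2. Ask both groups the same smoking question, covering cigarettes and marijuana, on the baseline demographic questionnaire that Table 1 already lists for each. Ask participants already assessed retrospectively.
3. Record formal exercise training in the last 3 months and respiratory infection in the last month for controls. Repeat the comparison without controls who would fail the patient criteria, as a sensitivity analysis.
4. State how the 3-month training exclusion and the 4-week GEAR entry window fit together.

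Changing control eligibility mid-study is not advised. By January 2023, 11 of 17 controls had completed, so a new rule would reach at most 17 − 11 = 6 and leave a control group recruited under two rules.

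The cost is one questionnaire item on smoking, two recorded items for controls and a re-run of planned comparisons. The restricted analysis loses about 3 to 9 patients and widens the standard error by about 2% to 6%. Answers from participants already assessed depend on re-contact and recall.
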